### Randomization

A sampling frame of a list of disadvantaged clusters was obtained from Caen University, Caen, France. Clusters (IRIS) will be randomly assigned to the 2 randomization groups in a 1:1 ratio using computer-generated simple randomization. Eligible women living in the randomly selected disadvantaged clusters will be identified using the Regional Cancer Screening Coordinating Centre of Occitanie (CRCDC-OC) database.

### Study Procedures

Eligible women in both groups will receive screening reminder letters and HPVss kits. The HPVss kit will contain a self-adhesive barcode, an HPVss kit, instructions with illustrations on how to self-collect the vaginal samples, and a postage-paid, preaddressed return envelope. Women in the experimental group will receive an information letter explaining the nature of the research, its objective, and what participants will be required to do and how to access the chatbot-based decision aid.

Participants in both groups will be requested to either perform vaginal self-sampling at their home (with the collection kit provided) or have an HPV test with their gynecologist, primary care physician, or midwife. Those who choose HPVss will be encouraged to contact the CRCDC-OC via telephone or email in the event of any uncertainty.

### HPV Test Analysis and Management of Results

Participating women in both groups will be asked to send the samples via regular mail to a centralized laboratory using the postage-paid envelope. The results will be communicated to the women, their primary care physician, and the CRCDC-OC generally within 2 weeks after the self-collected sample arrives at the centralized laboratory. Women with negative results will be advised to repeat CCS after 5 years. HPVss-positive women will be invited to consult their primary health physician, who will explain what a positive HPVss test result means and suggest further investigations in accordance with national guidelines [28].

HPVss-positive women will be referred for liquid-based cervical cytology triage:

HPVss-positive women with a cytological diagnosis of atypical squamous cells of undetermined significance or worse will be referred for colposcopy.HPVss-positive women with a normal cytological diagnosis will be advised to undergo HPV testing 1 year later. If this triage HPV test, performed 1 year later, yields positive results, colposcopy should be performed; if this triage HPV test yields negative results, another HPV test should be offered 5 years later.

For women with an uninterpretable HPV test, a new HPVss collection kit will be sent to them. If the second HPV test result is also uninterpretable, the women will be advised by mail to have an HPV test with a health professional as soon as possible.

The CRCDC-OC will track the HPVss-positive women to investigate whether they receive follow-up procedures in accordance with national recommendations and will recall women or providers, if necessary.

### Data Collection and Study Variables

The study data will be generated from the CRCDC-OC database. The source of the CRCDC-OC database is the French health insurance database (*Système National des Données de Santé*; SNDS). This database contains individualized and deidentified data on all medical expenditures and reimbursements. All medical care received in the public, private, or liberal sector is recorded in the SNDS. No additional personal or clinical information will be collected during this trial. Anonymized data for each individual participant will be received, stored, and handled at International Agency for Research on Cancer (IARC) using Research Electronic Data Capture, a secure, web-based software platform designed to support data capture for research studies [29,30]. All standard precautions will be taken to ensure the privacy and protection of personal and medical information. Only the principal investigators and coinvestigators as well as the data manager will have access to the data.

This database enables access to some data on women’s characteristics (date of birth, place of residence, and type of health insurance), screening (HPV testing), and further investigations (cytology, colposcopy, biopsy, treatment of precancerous lesions, and surgery).

Real-time usage statistics generated by the chatbot platforms will be used to evaluate women’s use of the chatbot. Chat volumes, response time to women’s chat requests, the number of queries resolved, the main topics in women’s requests, navigation flow, and women’s satisfaction will be analyzed.

### Primary Study Outcomes

The study has 2 primary outcomes: (1) the proportion of screening participation within 12 months among women recalled for CCS and (2) the proportion of HPVss-positive women who are “well-managed” as stipulated in the French guidelines. Both proportions will be compared between experimental and control groups, taking into account the stratification by age group, place of residence, and type of health insurance.

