### Sample Size

The sample size involved estimation of the number of clusters (IRIS) using a composite outcome, “well-managed” women, which is defined as those women who completed a valid HPVss test and were either advised of a negative result (in the case of HPVss-negative women) or completed the assessment (in the case of HPVss-positive women), and, where necessary, treatment pathway. The following assumptions were considered:

Expected average cluster size of 250 eligible women; this is an estimate of the number of women in the target age range (30-65 years) within a cluster of 2000 people, based on the population pyramid of ages in the Occitanie Region.Expected proportion of overall well-managed women in the control group of 15%.Expected absolute increase of 10% in the proportion of overall well-managed women in the experimental group.Coefficient of variation taking into account the possibility of varying cluster sizes of 1.2 (arrived at because of the wide level of dispersion around the mean cluster size) [26].A 10% precision in the proportion of overall well-managed women, which would lead to a 0.029 intracluster correlation using a beta-binomial model [27].A power of 80% and a 5% 2-tailed significance level.

Under the aforementioned assumptions, the required number of clusters to randomize in each arm would be 10 (total: 20 clusters). However, if subgroup analyses are to be performed, stratifying on general population density, medical density of the department (high or low), and setting of the community (rural or urban), taking into consideration these α adjustments (α=.3125% [2.5%/8]) for each of the subgroup analyses in order to be able to remain with a 5% 2-tailed significance level for the overall effect, approximately 16 clusters in each arm (32 clusters in total) will be required for the subgroup analyses.

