### Statistical Analysis

The participants’ categorical characteristics will be presented as proportions compared between the intervention and control groups using chi-square analysis. Continuous variables will be presented as median (interquartile range) values. Comparisons will be carried out using Kruskal-Wallis tests. The effect of the intervention on both the primary and secondary outcomes will be assessed using logistic regression models, adjusting for individual characteristics that are statistically significant in the univariate analysis and the cluster design. The effect estimates obtained from the regression analysis will be presented as odds ratios together with their 95% CIs. Just Another Gibbs Sampler software will also be used to model missing data in outcomes and/or explanatory variables [31].

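### Two primary outcomes are each compared at 5% with no rule across them; if either can support a claim, the chance of a false primary result is up to about 10%, not 5%

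*Protocol article*

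**What the plan says.** The Primary Study Outcomes section of the protocol article opens: "The study has 2 primary outcomes: (1) the proportion of screening participation within 12 months among women recalled for CCS". The second outcome is "2) the proportion of HPVss-positive women who are “well-managed” as stipulated in the French guidelines". It continues: "Both proportions will be compared between experimental and control groups". The Abstract gives the same two outcomes.

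The Statistical Analysis section uses one family of models throughout: "The effect of the intervention on both the primary and secondary outcomes will be assessed using logistic regression models". Effects "will be presented as odds ratios together with their 95% CIs". It has no step for multiplicity.

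Error rates appear only in the Sample Size section. The basic calculation uses "A power of 80% and a 5% 2-tailed significance level" and arrives at 10 clusters per arm. A further step, conditional on subgroup analyses being done, is described as "taking into consideration these α adjustments (α=.3125% [2.5%/8]) for each of the subgroup analyses". Its stated purpose is "in order to be able to remain with a 5% 2-tailed significance level for the overall effect". This step raises the number of clusters from 10 to 16 per arm.

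**The concern.** The Sample Size section treats the trial as having one overall effect to be protected at 5%. The Primary Study Outcomes section gives it two. Alpha is divided for the subgroup claims, which come second in importance, but not for the two primary claims. A reader cannot tell whether one significant primary outcome is enough, whether both are needed, or whether one is tested first.

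The Discussion expects a successful result to inform policy makers and lead to updated local guidelines. If the rule for success is left open, it could be settled after the results are known, in favour of whichever outcome was significant. The 5% stated in the Sample Size section would then not be the error rate of the primary claim.

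**Working it through.** **Inputs from the protocol article.** Two primary outcomes (Primary Study Outcomes); 95% intervals, hence 5% two-sided per outcome (Statistical Analysis). From Sample Size: 5% two-tailed, 80% power, 0.3125% per subgroup analysis, control proportion 15%, experimental proportion 15% + 10% = 25%, mean cluster size 250, intracluster correlation 0.029, coefficient of variation of cluster size 1.2. The correlation between the two primary test statistics is not given and is varied below as an assumption.

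**1. The plan's own alpha figure.** 2.5%/8 = 0.3125%, as stated. The 2.5% can be related to the 5% in two ways:
- 5% for the overall effect plus 8 × 0.3125% = 7.5% in total;
- 2.5% for the overall effect plus 8 × 0.3125% = 5% in total.

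The wording favours the first, because it keeps 5% for the overall effect. Neither divides anything between two primary outcomes.

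**2. Do the cluster counts show a split?** With equal cluster sizes the design effect is 1 + 249 × 0.029 = 8.22.
- Unpooled variance: n per arm = (z for alpha + z for power)² × (0.15 × 0.85 + 0.25 × 0.75)/0.10². This is 247.2 at 5% and 454.1 at 0.3125%. Clusters: 247.2 × 8.22/250 = 8.13 and 454.1 × 8.22/250 = 14.93. One extra cluster per arm gives 9.13 and 15.93, rounded up to 10 and 16.
- Pooled variance with no extra cluster: 303 per arm at 2.5% gives 9.96, and 460 per arm at 0.3125% gives 15.13, again rounded up to 10 and 16.

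The stated counts therefore fit either 5% or 2.5% for the overall effect, depending on convention, and cannot settle which was used. Both reproductions leave out the stated coefficient of variation of 1.2, which is a separate matter.

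**3. Chance of at least one false-positive primary result, each tested at 5% two-sided.** If independent: 1 − 0.95² = 0.0975. The ceiling under any dependence is 5% + 5% = 10%. For correlated tests it is 1 − P(|Z1| < 1.96 and |Z2| < 1.96) under a bivariate normal. The last column counts only false results in favour of the intervention, 1 − P(Z1 < 1.96 and Z2 < 1.96).

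| Assumed correlation | Either direction | Favouring the intervention |
|---|---|---|
| 0 | 9.75% | 4.94% |
| 0.3 | 9.51% | 4.76% |
| 0.5 | 9.07% | 4.54% |
| 0.7 | 8.35% | 4.17% |
| 0.9 | 7.04% | 3.52% |
| Single test, for comparison | 5% | 2.5% |

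**4. If both outcomes had to succeed.** A false claim would need the test of a truly null outcome to be significant along with the other, so its chance is at most 5%.

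**5. After a rule is set.** At 2.5% each: 1 − 0.975² = 4.94% if independent, and at most 5% in any case. In a fixed sequence at 5% each, if the first null hypothesis is true, no false claim arises unless the first test rejects (5%). If it is not true, only the second test can be false (5%). The total is at most 5%.

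**The case against.** The strongest reply is that this is a condensed article. Testing order and success rules often sit in a statistical analysis plan, which is not shown here. The Sample Size section is a calculation for a composite that matches neither primary outcome as worded, its subgroup step is conditional, and its alpha levels may be no more than sizing inputs. The article nowhere says that one significant outcome is enough.

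Much of this stands. The either-outcome rule is a scenario, and an unseen plan may exclude it. What does not stand is treating the point as mere missing detail. The article states an error rate for the trial and divides alpha to protect it, and that division does not cover the two primaries it names.

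The 2.5% might also be read as 5%/2 for two outcomes. The text ties it only to the eight subgroup analyses. If each primary took 2.5%, the 5% would be used up and nothing would be left for the subgroups.

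Three stronger readings are tempting but not supported:
- That the error rate simply is close to 10%. This needs near-independent tests and an either-outcome rule. The second outcome is confined to women with a positive self-sample, so low correlation is plausible, but the article gives no value.
- That the rate reaches 2 × 7.5% = 15% once subgroups are counted. This assumes all eight subgroup tests are run on each primary. The article ties its subgroup sizing to the composite, and subgroup claims are not primary claims.
- That the subgroup analyses must become exploratory. The two-outcome problem does not require it, and the subgroup analyses are the only reason given for 32 clusters rather than 20.

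**Conclusion.** The point holds in conditional form. As written, the article does not secure 5% across its two primary outcomes. If either can support a claim, the chance of at least one false-positive primary result is up to about 10%: 9.75% under independence, and about 9.5% down to 7% at assumed correlations of 0.3 to 0.9. Counting only errors in favour of the intervention, it is 4.9% against 2.5% for a single test under independence. If both outcomes must succeed there is no inflation, but that rule is not stated. The source of the 2.5% reserved for subgroups is unclear, and the cluster counts do not resolve it. This should be corrected, with the reservation that an unseen analysis plan may already contain the rule.

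**What to change.** Before results are seen, state one rule that holds 5% across the two primaries. Either of these would do:
- **Fixed sequence.** For example, test participation at two-sided 5%, then the well-managed outcome among women with a positive self-sample at 5% only if the first is significant. The order is the investigators' choice. The primary objective is framed around participation in the care pathway, which makes participation a natural first test but does not compel it.
- **Split.** Test each outcome at 2.5% two-sided and report intervals to match.

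In the same place, state how the 2.5% set aside for the subgroups relates to the 5%.

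The cost is a sentence or two, and error control needs no extra clusters. Under the sequence, the second outcome can be claimed only if the first is significant. Under the split, each test loses some power. For the sizing composite, the unpooled convention above at 2.5% gives 299.4 × 8.22/250 + 1 = 10.85, so 11 clusters per arm, within the 16 planned. If the coefficient of variation of 1.2 is included, the design effect is 1 + ((1.2² + 1) × 250 − 1) × 0.029 = 18.66, and power with 16 clusters per arm falls from about 74% at 5% to about 64% at 2.5%. These figures are for the composite and do not carry over to either primary outcome.

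### Primary outcome 2 is restricted to HPVss-positive women, a group formed after randomization and not the one the trial was sized on, so it is neither a randomized comparison nor covered by the stated 80% power

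*Protocol article*

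**What the plan says.** Protocol article, Primary Study Outcomes (repeated in the abstract's Methods), names two primary outcomes. The first is "the proportion of screening participation within 12 months among women recalled for CCS". The second is "the proportion of HPVss-positive women who are" well-managed under the French guidelines.

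Sample Size uses the same label for something else. It states: "The sample size involved estimation of the number of clusters (IRIS) using a composite outcome". That composite consists of "those women who completed a valid HPVss test and were either advised of a negative result" or, if positive, completed the assessment and any treatment needed. The planning values are "Expected proportion of overall well-managed women in the control group of 15"%, "Expected absolute increase of 10% in the proportion of overall well-managed women in the experimental group" and "Expected average cluster size of 250 eligible women", with an intracluster correlation of 0.029, a value of 1.2 for varying cluster size, 80% power and a two-tailed 5% level. The result is 10 clusters per arm, raised to 16 for subgroup analyses.

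Objectives and Endpoints states that the intervention is meant to improve participation in the self-sampling pathway. Statistical Analysis plans logistic regression adjusted for individual characteristics and the cluster design. The women's characteristics listed under Data Collection and Study Variables are date of birth, place of residence and type of health insurance.

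**The concern.** Two different quantities share one name. In the sized composite, all eligible women are the denominator and a woman with a notified negative result is a success. In primary outcome 2, only HPVss-positive women are counted and a negative woman does not appear.

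This has two consequences.

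- **Selection.** HPVss-positive status arises after allocation and depends on returning a kit. If the chatbot brings in women who would otherwise not have tested, the experimental arm's positives are a different mix from the control arm's. A difference in follow-up between arms then combines any effect on follow-up with a change in who is being followed. Age, residence and insurance type do not measure reluctance to attend, so the planned adjustment cannot be relied on to restore comparability.
- **Power.** The article gives no expected rate, effect or power for the HPVss-positive group, which is a small fraction of the women in the power statement. A null result on a primary outcome could be read as evidence of no effect when the trial had little chance of showing one.

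**Working it through.** **1. Which outcome the plan's cluster numbers belong to.** Inputs from Sample Size: 15%, 25%, cluster size 250, intracluster correlation 0.029, and 1.2.

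- Two proportions, two-sided 5%, 80% power (pooled-variance formula): n = 250 per arm before clustering.
- Reading 1.2 as a multiplier on cluster size, the design effect is 1 + (1.2 × 250 − 1) × 0.029 = 9.67. Clusters per arm = 250 × 9.67 / 250 = 9.67, so 10.
- At 0.3125% per tail, n = 408, and 408 × 9.67 / 250 = 15.78, so 16.

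Both stated figures reproduce for the composite over all eligible women. A literal coefficient of variation of 1.2 gives a design effect of 1 + ((1 + 1.44) × 250 − 1) × 0.029 = 18.66 and 19 clusters per arm, which does not match. That is a separate point to clarify.

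**2. Selection (assumed values).** Let 15% return a kit in either arm, and let the chatbot add 10%. Assume equal positivity and no effect on any woman's follow-up. The control proportion is f0; the experimental proportion is (15 × f0 + 10 × f1) / 25, where f1 is the completion rate among positives in the added women.

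- f0 = 80%, f1 = 60%: (15 × 0.80 + 10 × 0.60) / 25 = 72% against 80%, an apparent loss of 8 points.
- f0 = 60%, f1 = 80%: (15 × 0.60 + 10 × 0.80) / 25 = 68% against 60%, an apparent gain of 8 points.

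**3. Size of the HPVss-positive group.** Positivity is not in the article; 10–15% is assumed. The composite's 15% and 25% are used as the proportions tested.

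- 16 × 250 = 4000 women per arm: 4000 × 0.15 × (0.10 to 0.15) = 60–90 control positives; 4000 × 0.25 × (0.10 to 0.15) = 100–150 experimental positives.
- The abstract's figure of about 4000 women can also be read as the trial total. With 2000 per arm the counts halve, to 30–45 and 50–75.

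**4. Power for primary outcome 2.** Assumed gain of 10 points, two-sided 5%, no clustering. Power = Φ(0.10 / SE − 1.96), where SE = √[p1(1 − p1)/n1 + p2(1 − p2)/n2]. The 41% baseline is the lower of the two French follow-up figures in the Introduction; 80% is assumed, since a 10-point gain from the upper figure of 92% is impossible.

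| Women per arm | Lowest case: 10% positivity, 41% to 51% | Highest case: 15% positivity, 80% to 90% |
|---|---|---|
| 4000 | SE 0.0808, power 23% | SE 0.0488, power 54% |
| 2000 | SE 0.1143, power 14% | SE 0.0690, power 31% |

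Widening positivity to 8–20% and adding a design effect at 0.029, under either reading of 1.2 (pooled-variance formula), gives 16–59% with 4000 per arm and 11–39% with 2000. A 20-point gain (41% to 61%, or 60% to 80%) with 4000 per arm and 15% positivity reaches 86–91% without clustering and 69–85% with it.

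**5. How close the composite is to participation.** Composite / proportion tested = 1 − h(1 − f), with positivity h and follow-up f. Lowest: 1 − 0.15 × 0.59 = 0.91. Highest: 1 − 0.10 × 0.20 = 0.98. Treating 15% as the proportion tested in step 3 is therefore slightly low (15 / 0.91 = 16.5% at most), which does not alter the conclusion.

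**The case against.** The strongest reply is that primary outcome 1 uses all recalled women, matches the main objective and is untouched by the selection argument. Follow-up of positive women is a real concern that the Introduction documents (41% against 92% in two French studies), so a wish to test it is understandable. The numerical inputs are also not the plan's. Positivity, the follow-up split and the 10-point target are assumptions, and about 20 points could reach 80% power in favourable conditions. All of this stands. It limits how firmly the size can be stated, but it does not make the denominator a randomized one or transfer the power statement to it.

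A reader might infer four stronger things that the article does not support.

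- **That the intervention itself creates the subset.** Both arms receive kits, so positives arise in the control arm too. The supportable claim is that the chatbot may change who enters.
- **That the outcome will show spurious harm.** Neither the direction nor the size of the bias is established; step 2 of the working gives both signs.
- **That the chatbot will move women between kit and clinician.** Women in both arms may "have an HPV test with their gynecologist, primary care physician, or midwife", but nothing in the article indicates or quantifies such a shift, and a kit-based outcome fits the stated self-sampling pathway.
- **That the sharing of the 5% level between two primary outcomes is missing.** This is commonly left to a statistical analysis plan, which is not shown.

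**Conclusion.** The point holds in two parts that rest on the text alone. First, primary outcome 2 conditions on a post-randomization group whose membership the intervention may change, so its contrast should not be read as a randomized effect. Second, the 10 and 16 clusters per arm are for a composite over all eligible women, so the stated 80% power does not apply to primary outcome 2.

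The sizes are illustrative: 8 points of bias in either direction under assumed compliance, and power of about 23–54% (4000 women per arm) or 14–31% (2000 per arm) for an assumed 10-point gain, before clustering. Only larger effects, of about 20 points, could reach 80%, and then only with 4000 women per arm and positivity toward the upper end of the assumed range. The counts would be lower still if the 250 women per cluster are all women aged 30–65, as Sample Size describes them, and not only those overdue for screening.

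**What to change.** Reconcile Sample Size with Primary Study Outcomes and the abstract:

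1. Define primary outcome 2 as the composite already given under Sample Size, with all recalled women in the randomized clusters as denominator.
2. Report well-managed among HPVss-positive women as a secondary, descriptive outcome, and state that it is not interpreted as a randomized effect.
3. State that the power figure refers to the composite.

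Counting clinician-taken HPV tests in the composite is optional and a choice of estimand for the investigators.

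**Cost.** The change is to the wording of the article and the registration; the same regional screening database supplies the data. The real price is scientific. Under the assumptions above the composite is about 91–98% of the proportion tested, so it largely overlaps primary outcome 1 (less so if many women in that outcome choose a clinician test), and follow-up of positive women loses its confirmatory test. If the investigators consider a near-duplicate second primary of little use, making the current outcome 2 secondary without a replacement would also remove the selection problem. Sample Size would then have to say how its figures relate to primary outcome 1.
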